## 4.3 Loss to follow-up

Every effort will be made to trace patients not returning to the centre for follow-up visits. Home visits will be carried out by a team member for cases who do not attend for follow-up.

A patient will be considered lost to follow up if she/he does not come for follow up and cannot be found by D42 of their schedule. Missing some follow up visits but reappearing before or on study D42 is not considered lost to follow up.

The time-window allowed for routine follow up visits:

- study day7 is +1 day
- study days 14 – 42 is -1, +2 days

## 4.4 Unscheduled visits

Patients presenting to the clinic with a fever or other symptoms on unscheduled days will be assessed by the study physician. Their temperature will be recorded, a blood smear will be made and the Hb measured by HemoCue. Patients will be treated as clinically indicated and will continue study procedures. Data from unscheduled visits will be recorded in the CRF and will be analysed.

## 4.5 Protocol deviations & violations

A protocol deviation is a departure from the approved protocol that does *not* result in harm to the trial patients whereas a violation is potentially harmful.

Protocol deviations include:

- the patient took an antimalarial drug not prescribed by the research team
- giving PQ at the wrong time
- Hb not being measured as per schedule
- delay in reporting SAE
- consent form not properly signed

Protocol violations include:

- enrolment violation – a patient who was wrongly included in the study
- patient was enrolled without signing the consent form
- the wrong dose of study drug/s was/were given

- misreading a negative malaria as positive resulting in patients receiving rescue treatment
- the patient was given (either by the research team or from another source) a drug (other than PQ/placebo) known to cause haemolysis in G6PDd

Protocol deviations and violations will be recorded on the protocol deviation/violation form and reported to the DMEC.

## 5 STUDY DRUGS

### 5.1 Artemether lumefantrine

AL is the recommended first line drug for falciparum malaria in DRC and Uganda.

GMP manufactured AL will be obtained from a reliable manufacturer or official supplier either locally or externally and imported. If imported all necessary documentation will be obtained (e.g. certificate of analysis, etc). AL will be dosed by weight, in accordance with the manufacturer's recommendation. One tablet of dispersible and non-dispersible AL contains 20 mg of artemether and 120 mg of lumefantrine.

AL is dose twice daily. On the first day of treatment the doses are separated by 8 hours but by 12h on the second and third days of treatment. The total course is 6 doses.

| Weight in kg | Number of tablets / dose | Total number of tablets / day | Total number of tablets / course |
|--------------|--------------------------|-------------------------------|----------------------------------|
| 5 - <15      | 1                        | 2                             | 6                                |
| 15 - < 25    | 2                        | 4                             | 12                               |
| 25 - < 35    | 3                        | 6                             | 18                               |
| ≥ 35         | 4                        | 8                             | 24                               |

### 5.2 Dihydroartemisinin piperazine

DHAPP has been extensively used in Africa and Asia and the Sigma Tau formulation is registered in several African countries and was registered in the European Union in 2011.

GMP produced DHAPP will be obtained from a reliable source and, if imported, all necessary documentation will be obtained. DHAPP will be dosed by weight. The 2015 WHO guidelines now recommend a dose of  $\geq 2.5$  mg/kg/day of DHA in children who weigh  $< 25$  kg (<http://www.who.int/malaria/publications/atoz/9789241549127/en/>).

There are three DHAPP tablet strengths, all in mgs:

- DHA 20 PP 160
- DHA 40 PP 320
- DHA 80 PP 640

The teams will modify the WHO dosing chart according to the tablet strengths they are able to obtain in Kinshasa and Uganda.

Table 1. DHAPP dosing table from the WHO.

| Body weight (kg) | Dihydroartemisinin + piperaquine dose (mg) given daily for 3 days |
|------------------|-------------------------------------------------------------------|
| 5 to < 8         | 20 + 160                                                          |
| 8 to < 11        | 30 + 240                                                          |
| 11 to < 17       | 40 + 320                                                          |
| 17 to < 25       | 60 + 480                                                          |
| 25 to < 36       | 80 + 640                                                          |
| 36 to < 60       | 120 + 960                                                         |
| 60 < 80          | 160 + 1280                                                        |
| >80              | 200 + 1600                                                        |

### 5.3 Primaquine/placebo

PQ/placebo (2.5, 5, 7.5 mg PQ base) will be manufactured for this trial by Centurion Remedies, PVT Ltd, Gorwa, India. This is a WHO certified manufacturing facility. Bilcare Ltd, Pune, India, will blister pack the PQ/placebo and will manage their export from India to the DRC and Uganda, in accordance with all applicable drug regulations.

Bilcare Ltd has already supplied quality, GMP manufactured PQ/placebo for MORU for another large trial (NCT01814683). The batch of PQ/placebo used for this trial will be quality controlled and a certificate of analysis will be supplied by Bilcare Ltd.

Dosing will be by age. The target dose of PQ is 0.25 mg/kg with a therapeutic dosing range of 0.15 - 0.4 mg/kg given once with the first dose of AL or DHAPP. Children will receive doses ranging from 0.1 - 0.46 mg/kg. A detailed breakdown of the mg/kg dose that a child will receive is shown in Table 2.

For young children who cannot swallow, the PQ/placebo tablet will be dissolved in 5 mL of sugar water (or similar solution depending on local practice) and the dose administered. The 2.5 mg PQ/placebo tablet will be used for children aged 6-11m but they will be given 2.5 mL of suspension and so will receive 1.25 mg of PQ/placebo. Guidelines on the practicalities of drug administration will be written.

Table 2. Dosing table by age of PQ showing the mg/kg dose received.

| Age   | Primaquine dose in mg base | minimum | 1 st quartile | median | 3 rd quartile | Maximum |
|-------|----------------------------|---------|--------------------------|--------|--------------------------|---------|
| 6-11m | 1.25                       | 0.1     | 0.15                     | 0.16   | 0.18                     | 0.3     |
| 1y    | 2.5                        | 0.16    | 0.25                     | 0.27   | 0.3                      | 0.46    |
| 2y    | 2.5                        | 0.14    | 0.2                      | 0.22   | 0.25                     | 0.37    |
| 3y    | 2.5                        | 0.12    | 0.17                     | 0.19   | 0.21                     | 0.32    |
| 4y    | 2.5                        | 0.11    | 0.16                     | 0.17   | 0.19                     | 0.29    |
| 5y    | 2.5                        | 0.1     | 0.15                     | 0.16   | 0.18                     | 0.25    |
| 6y    | 5                          | 0.17    | 0.26                     | 0.29   | 0.32                     | 0.44    |
| 7y    | 5                          | 0.16    | 0.24                     | 0.26   | 0.29                     | 0.39    |
| 8y    | 5                          | 0.14    | 0.21                     | 0.24   | 0.26                     | 0.34    |

|     |     |      |      |      |      |      |
|-----|-----|------|------|------|------|------|
| 9y  | 5   | 0.12 | 0.2  | 0.21 | 0.24 | 0.3  |
| 10y | 7.5 | 0.17 | 0.26 | 0.29 | 0.32 | 0.4  |
| 11y | 7.5 | 0.16 | 0.24 | 0.27 | 0.29 | 0.36 |

#### 5.4 Drug supervision

All doses of study drugs will be administered by research nurses. A small snack or milk will be given with every dose to reduce the risk of PQ induced abdominal pain and to increase the absorption of lumefantrine and piperazine.

The study patients will be observed for 60 min. Any patient who vomits during this observation period will be retreated with the same dose of AL, DHAPP and PQ/placebo (and observed for an additional 30 min).

If the vomiting occurs between 31 and 60 minutes, patients will receive an additional:

- half dose of AL or DHAPP
- half dose of PQ/placebo

If the patient vomits again, oral treatment will be stopped and parenteral rescue therapy will be given (See Section 6).

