### 3.10.3 Balancing recruitment numbers

Data from Kinshasa and Uganda show that children aged 6-11 months and those aged 5-11 years are relatively under represented. We will, therefore, review periodically the distribution of ages of our recruited patients from both sites combined and will aim to recruit a total of at least:

- 80 children aged 6-11m and
- 120 children aged 5-11 years.

This may require a temporary suspension of the recruitment of some age group as the trial proceeds.

### 3.10.4 Option to dose primaquine/placebo on Day 1

Data show that early vomiting within one hour can affect a significant minority of patients when treated for falciparum malaria. Children under five are most affected and rates within the under 5s are inversely related to age .

Pooled data from the World Wide Antimalarial Resistance Network show rates of early vomiting with DHAPP ranging from 3-18% on Day 0 compared to 1-9% on Day 1. Corresponding rates in AL treated children aged < 5 are from 2.3-7.3% and 0.5-6%. These data are consistent with the experience from KIMORU .

Initially, we will dose all children on Day 0 and record rates of early vomiting (indeed this is an adverse event of interest – see Section 8).

When approximately half of the patients have been recruited, we will analyse the data and consider whether we wish to dose PQ/placebo on Day 1.

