### 3.10.5 Patients not completing treatment

Patients may not complete their treatment for the following reasons:

- persistent vomiting of study drugs. A patient who vomits his/her AL or DHAPP +/- PQ/placebo within one hour and also the repeat dose/s will be given rescue treatment and when better will continue follow up to D42 (see Section 6).
- the development of an adverse / serious adverse event necessitating the early stopping of study drugs; these patients will remain in the study to D42
- the PI withdraws the patient from the study before treatment is completed (see Section 4.1).

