#### 12.3.2 Dihydroartemisinin piperazine

DHAPP has been used extensively in China and more recently in Africa and Asia. It has an excellent safety record and is very well tolerated. Side effects are reported with quite marked ranges in different studies and include:

- early vomiting which is higher in younger children aged < 5y. Rates of 18 to 3% have been reported in children aged <1y and aged 4-5y, respectively.
- vomiting leading to a change in treatment is also dependent on age and was 3.8% in Ugandan children aged 6 to 24 months
- anorexia 11%
- nausea, diarrhoea, abdominal pain 3-10%
- headache 23%
- dizziness 1.5-17%
- poor sleep 14%
- itching 1-2%
- urticaria 1%

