#### 12.3.3 Primaquine

PQ is also generally well tolerated. The main side effects are abdominal pain which is dose related and improved by taking PQ with food. Rates of abdominal pain and/or cramps were 3% (15 mg/d), 12.5% (22.5 mg/d), 10% (30 mg/d) and 5/7 (60 mg/d).

PQ converts haemoglobin (Hb) to methaemoglobin (metHb). Blue discolouration around the lips may be seen when metHb concentrations are between 15-20 g/L, equivalent to ~10-20% of the Hb concentration. It is rare - only one case was found in 3,000 American soldiers on 15 mg of daily for 14 days.

MetHb levels exceeding 10% with PQ doses of 15 or 22.5 mg/day in adults are unusual; levels of 16-18% were found in three (6.5%) of 46 Australian soldiers. In vivax infected Cambodians, the maximum metHb after one dose of DHAPP and one dose of 45 mg of PQ was 4.9% with a significantly (p<0.001) lower median value in the G6PDd (0.7%) vs. the G6PD normal (1.7%) patients ([name], unpublished).

There are reports of both increases and decreases in the total white cell counts but the clinical significance of these findings is unclear; some patients also received myelotoxic drugs or had diseases characterised by myelosuppression are additional risk factors.

The most important side effect of PQ is AHA in individuals with G6PD deficiency. Its severity is related to the degree of G6PD deficiency and the PQ dose. Haemolysis is less severe in the African (A) G6PD variant compared to the Asian and Mediterranean variants.

In *P. falciparum* infected Tanzanian children [all with haemoglobin (Hb) concentrations > 8g/dL], 0.75 mg/kg of PQ caused a fall in the mean Hb concentration in all patients that was higher in G6PDd patients: -2.5 (G6PD A- hemizygous or homozygous) vs. -1.6 (G6PD A- heterozygotes) vs. -0.5 g/dL (G6PD B / wild type homozygous). In this study, the target PQ dose was 0.75 mg/kg but many patients received a PQ dose exceeding this.

Our study will be using SLDPQ; the target dose 0.25 mg/kg and maximum dose will be 0.45 mg/kg in children aged 1 year. Therefore, we expect smaller falls in Hb compared to the Tanzanian study.

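### Section 5.4 gives two re-dosing rules for vomiting at 31–60 minutes, a full repeat and a half dose, so the repeat primaquine dose is left open by a factor of two

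*Protocol*

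**What the plan says.** Section 5.4 of the protocol makes three statements in sequence.

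- On the window: "The study patients will be observed for 60 min".
- On vomiting within it: "Any patient who vomits during this observation period will be retreated with the same dose of AL, DHAPP and PQ/placebo".
- On the second half of it: "If the vomiting occurs between 31 and 60 minutes, patients will receive an additional" half dose of AL or DHAPP and half dose of primaquine/placebo.

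The only other text on repeat dosing is in Section 3.10.5: "A patient who vomits his/her AL or DHAPP +/- PQ/placebo within one hour and also the repeat dose/s will be given rescue treatment". It uses the same one-hour window and gives no amount for the repeat.

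Section 5.3 puts the primaquine a child will receive at 0.1–0.46 mg/kg and does not say whether that includes re-dosing. Section 12.3.3 says of primaquine-induced haemolysis in G6PD deficiency: "Its severity is related to the degree of G6PD deficiency and the PQ dose".

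**The concern.** The full-repeat rule covers any vomiting in the 60-minute period, with no lower time limit. The half-dose rule covers minutes 31–60 of the same period. Both therefore apply to the same child, and they order different amounts of both the ACT and primaquine/placebo.

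This is a safety trial of one low primaquine dose, and its population of main interest is G6PD-deficient children. The protocol itself ties the severity of haemolysis to dose. An instruction that can be followed in two ways, one giving twice the repeat dose of the other, leaves exposure to the reading of the nurse giving the dose. It also leaves a monitor without a standard: Section 4.5 lists giving the wrong dose of study drug as a protocol violation, but for these children the protocol does not fix the right dose.

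The comparison of primaquine with placebo is not biased by this, because placebo recipients are re-dosed under the same text and the allocation is blinded.

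**Working it through.** The plan has no figure of its own to reproduce here. The check is a reading of the two rules followed by arithmetic on Table 2.

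**Overlap.** Same-dose rule: minutes 0–60. Half-dose rule: minutes 31–60. Overlap: minutes 31–60, which is the whole of the second rule's range.

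**Repeat dose for vomiting at 31–60 minutes.** Same-dose rule = 1.0 × nominal dose; half-dose rule = 0.5 × nominal dose. Nominal doses are from Table 2.

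| Age | Same-dose rule (mg) | Half-dose rule (mg) | Ratio |
|---|---|---|---|
| 6–11 months | 1.25 | 0.625 | 2.0 |
| 1–5 years | 2.5 | 1.25 | 2.0 |
| 6–9 years | 5 | 2.5 | 2.0 |
| 10–11 years | 7.5 | 3.75 | 2.0 |

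**Difference in mg/kg** = 0.5 × the Table 2 value.

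- 1-year row, median: 0.5 × 0.27 = 0.135 mg/kg
- 1-year row, maximum: 0.5 × 0.46 = 0.23 mg/kg
- Medians across all ages (0.16 to 0.29): 0.08 to 0.145 mg/kg

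**Total administered**, first plus repeat dose and before any loss by vomiting: 2.0 × nominal against 1.5 × nominal, a ratio of 2.0/1.5 = 1.33.

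- 1-year median: 2 × 0.27 = 0.54 against 1.5 × 0.27 = 0.405 mg/kg
- 1-year maximum: 2 × 0.46 = 0.92 against 1.5 × 0.46 = 0.69 mg/kg

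**Number of children.**

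- Section 11.1 plans 800 G6PD-deficient patients. With equal allocation, 800/2 = 400 receive primaquine, about 200 with each ACT.
- Section 3.10.4 reports "early vomiting with DHAPP ranging from 3-18% on Day 0 compared to 1-9% on Day 1". For AL in children under 5 it gives 2.3–7.3% on Day 0.
- DHAPP: 200 × 3% = 6 to 200 × 18% = 36.
- AL: 200 × 2.3% = 4.6 to 200 × 7.3% = 14.6.
- Total early vomiters: 10.6 to 50.6.
- The share at 31–60 minutes is not in the protocol. Assuming 25–75%: 10.6 × 0.25 = 2.7 to 50.6 × 0.75 = 38.0.

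The upper end is likely too high. It applies 18% to every DHAPP child, whereas Section 12.3.2 says: "Rates of 18 to 3% have been reported in children aged <1y and aged 4-5y, respectively". It also applies the AL under-five rates to all ages.

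**The case against.** The best defence is that the second sentence is a specific exception to the first. If the same dose were meant for the whole hour, the 31–60 minute rule would have no purpose. The amendment history records that the observation time was lengthened from 30 to 60 minutes, which may be how a rule written for the first half hour came to cover the whole hour. On that view a time limit is missing, and there are not two competing policies. This is probably the intent. It is still an inference that the text does not state, and the word *additional* allows a third reading, a half dose on top of the full repeat.

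Sections 5.3 and 3.10.2 promise separate guidelines on drug administration and drug management, and all doses are given by research nurses, so practice may be uniform. Those guidelines are not available here. They would have to choose between two protocol sentences and could not correct either.

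On size, three points are fair. The two-fold ratio applies to the repeat dose; total drug given differs by 1.33, and the amount retained is unknown. A full repeat is already accepted for vomiting in the first 30 minutes, so the higher reading introduces no new dose level. The headcount rests on an assumed share, and a move to Day 1 dosing, which Section 3.10.4 allows, would lower the vomiting rates. These points limit the consequence. They leave the contradiction in place.

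Haemoglobin monitoring by the DMEC (Sections 3.10.6 and 9) should help detect harm, but it does not tell a nurse which dose to give.

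**Conclusion.** The concern holds. As written, Section 5.4 prescribes both a full and a half repeat dose for vomiting at 31–60 minutes, and no other section resolves it. The two-fold difference in the repeat dose follows directly from the text and Table 2 and needs no assumption.

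The number of children affected is uncertain. The range of about 3–38 among G6PD-deficient primaquine recipients depends on equal allocation, on the protocol's quoted vomiting rates applying to all ages, and on the assumed 25–75% share. The conclusion does not depend on that count.

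The consequence is for patient safety and consistent dosing. Because the conflict also covers the ACT, it reaches every treatment group. Non-inferiority testing and sample size are unaffected.

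**What to change.** In Section 5.4, limit the full repeat of ACT and primaquine/placebo to vomiting at 0–30 minutes. For vomiting at 31–60 minutes, specify a half dose only and delete the word *additional*. The clinical leads should confirm that this is the intended rule before the text is changed.

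Two small additions would help, though the correction does not depend on them. Section 5.3 could state that the 0.1–0.46 mg/kg range excludes re-dosing. The CRF should capture the time of vomiting and the mg of primaquine/placebo re-given, if it does not already.

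The cost is one corrected sentence, one clarifying sentence and at most two CRF fields, with no change to the sample size or the analysis.

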#### 5.5 Concomitant drugs that must not be prescribed

Patients and guardians will be asked not to visit local pharmacies, doctors and drug vendors to buy drugs or herbal medicines, in case they take drugs that can cause AHA in G6PDd.

Below is a list of drugs that may cause AHA in G6PDd and are contraindicated in this study:

Potentially haemolytic drugs are listed below.

- Dapsone
- Sulphonamides
- Methylene blue
- Nalidixic acid
- Nitrofurantoin
- Niridazole
- Aspirin
- Traditional medicines

The following drugs may have a possible risk of haemolysis:

- Ciprofloxacin, norfloxacin
- Chloroquine

The following drugs are considered to be of doubtful risk of haemolysis:

- Chloramphenicol
- Quinine

#### 5.6 Concomitant drugs that are allowed

Febrile patients can be treated with paracetamol (acetaminophen). During follow-up, infections other than malaria may require the administration of medicines with antimalarial activity. This is allowed.

All drugs that are taken by patients will be noted on the Concomitant drug form and any details of adverse events (AEs) noted on the AE CRF.

### **5.7 Concomitant drugs that may interfere with primaquine**

The following drugs may increase the exposure of PQ, piperaquine and lumefantrine metabolism by inhibiting the cytochrome (CYP) 450 and should not be prescribed by the research team unless clinically essential:

- Ketoconazole, itraconazole
- Cimetidine
- Grapefruit juice
- Erythromycin
- Ritonavir

The following drugs may decrease the exposure of PQ, piperaquine and lumefantrine metabolism by inducing CYP 450. They should not be prescribed by the research team unless clinically essential:

- Barbiturates
- Carbamazepine
- Phenytoin
- Rifampicin
- Macrolide antibiotics
- Glucocorticoids

The following drug classes are metabolised by CYP 2D6 and may compete with PQ. They should not be prescribed by the research team unless clinically essential:

- tricyclic antidepressants e.g. amitriptyline
- major tranquilisers: haloperidol
- atypical antipsychotics: risperidone
- selective serotonin reuptake inhibitors: paroxetine
- beta blockers e.g. carvedilol, metoprolol
- opiates: codeine, tramadol
- antimalarials: pyronaridine

The following drugs are CYP2D6 inhibitors and may reduce the concentrations of PQ's active oxidative metabolites. They should not be prescribed by the research team unless clinically essential:

- amiodarone
- cimetidine
- diphenhydramine, terbinafine
- fluoxetine, paroxetine

- quinidine
- ritonavir

## 6 RESCUE TREATMENT

### 6.1 Parenteral rescue treatment

Parenteral rescue treatment will consist of intravenous or intramuscular artesunate and will be given for the following clinical indications:

- Persistent vomiting of study drugs
- The development of severe malaria/danger signs at any time during the study.

Parenteral artesunate is the preferred rescue treatment, followed by artemether. Quinine is the third choice.

### 6.2 Oral rescue treatment

Patients will be treated with oral amodiaquine-artesunate or a different ACT according to National Guidelines if they:

- fail to either clear their *P. falciparum* parasites within the first 7 days or
- develop asymptomatic or symptomatic recurrent malaria during the follow-up

All patients who require rescue treatment will be followed-up until study Day 42.

